## Abstract

**Background:**

Depression is a major public health problem with a rising prevalence and a negative impact on quality of life, mortality, and morbidity. While effective treatments, such as behavioral activation, are available, they are only effective for approximately half of the patients. Adherence to activities between therapy sessions is associated with better outcomes in behavioral activation, yet adherence rates could be improved. Just-in-time adaptive interventions (JITAIs) offer the potential to improve adherence to activities and thus improve outcomes in behavioral activation for depression; however, to date, they have not yet been studied.

**Methods:**

This mixed-methods study uses a participatory design phase with 12 participants with depression and 4 therapists to develop JITAIs for behavioral activation in depression, through focus groups and thematic analyses to answer the specific design question. A subsequent evaluation phase consists of a micro-randomized trial to assess the proximal effects of JITAIs and a nonrandomized quasi-experimental design to evaluate the feasibility and changes in distal outcomes compared with treatment as usual (TAU). Participants diagnosed with depression will be recruited from a mental health institution: 52 receiving TAU plus JITAIs and 52 receiving TAU only. The primary outcome is feasibility, and JITAIs are considered feasible when the dose-received adherence rate is greater than 60%. The secondary outcomes are acceptance as measured via the System Usability Scale, the Client Satisfaction Questionnaire and the Twente Engagement with E-health Technologies Scale. Ecological momentary assessments of depression and well-being are used as proximal outcomes, and the Patient Health Questionnaire-9, the Mental Health Continuum–Short Form, the Questionnaire about the Process of Recovery, and the EuroQol-5 Dimension are used as distal outcomes at the end of treatment.

**Discussion:**

This study aims to develop and evaluate JITAIs to support behavioral activation in the treatment of depression. If feasible, JITAIs have the potential to be further examined in randomized controlled trials and benefit people with depression by providing a scalable way to improve adherence and outcomes in behavioral activation.

**Trial registration:**

The Netherlands Clinical Trial Register (NL-OMON57144), prospectively registered on October 22, 2024.

**Supplementary Information:**

The online version contains supplementary material available at 10.1186/s40814-026-01835-5.

## Background

Depression is a major public health problem, with a rising prevalence and negative impact on quality of life, mortality, and morbidity [1]. Several effective treatments are available, including medication and psychological treatments. Although treatments are effective, they appear to be effective for only approximately half of the participants [2, 3]. These findings indicate that further research is needed to improve the treatment of depression.

Behavioral activation is one of the recommended psychological treatments for depression. While it is the behavioral component of cognitive behavioral therapy (CBT), it has also developed into a stand-alone treatment that can be as effective as the full CBT package [4, 5]. Behavioral activation encourages individuals with depression to seek activities that are expected to result in a sense of pleasure, mastery, or accomplishment. Examples of behavioral activities include gardening, walking, swimming, watching TV, cooking a favorite meal, reading a book, and talking about sports. Strategies such as monitoring mood, identifying pleasurable activities, and planning activities are used to achieve this goal. Meta-analyses have shown a large effect of behavioral activation on depressive symptoms [6], and several studies have shown that behavioral activation can be effectively implemented by a variety of trained disciplines [7–9].

Although behavioral activation is as effective as other treatments, including CBT, it benefits only half of the participants [2]. Participants who adhere to activity planning between sessions generally experience better treatment outcomes and fewer symptoms (small-to-moderate effect size) than those who perform fewer or no activities do [10–13]. However, adherence between sessions is far from ideal, with studies showing that only 47% of activities are completed and 27% are never attempted [14]. The main barriers to adherence were difficulty in selecting appropriate activities and problems while performing them, including perceived difficulty, lack of opportunity, and fear or avoidance [15]. From a behavioral activation perspective, such withdrawal and avoidance reduce contact with reinforcing experiences, thereby maintaining depressive symptoms. Interventions that support the start of small, feasible, and personally meaningful activities may help disrupt avoidance cycles and increase opportunities for pleasure and mastery [5]. Adherence to activities between sessions can be increased by discussing potential barriers between patients and therapists, involving patients in activity selection, and using reminders [16]. Although adherence to activities related to behavioral activation may increase its effects, it remains a significant challenge [6]. This gap in treatment adherence suggests the need for innovative approaches to support individuals more effectively between sessions in their daily lives.

Just-in-time adaptive interventions (JITAIs) offer a promising approach by providing context-specific support to improve adherence in participants’ daily lives. JITAIs use ecological momentary assessment and intervention (i.e., repeated measurements and delivery of interventions in daily life) to adapt to daily fluctuations in an individual’s state and context. The use of smartphones offers new opportunities for the real-time collection of data from everyday life, such as subjective experiences (e.g., symptoms, cognitions, emotions, and behaviors), context (e.g., location and activity), and the provision of interventions when an individual needs support [17–19]. JITAIs targeting alcohol use, physical activity, smoking, and anxiety symptoms have shown promising results [20]. However, no study has yet developed or evaluated JITAIs for behavioral activation in people with depression [21].

In our view, JITAIs are particularly suitable for behavioral activation because of the use of smartphones in everyday life, the possibility of providing personalized support with minimal or no supervision, and the use of reminders that may improve adherence. To improve our chances for the successful development of JITAIs, we will adhere to the design principles developed by Nahum-Shani and colleagues [19]. Following these principles, JITAIs for behavioral activation should consist of the following key components: decision points (e.g., moments when low mood is detected), intervention options (e.g., prompts to engage in pleasurable or meaningful activities), tailoring variables (e.g., self-reported mood tracked via momentary assessments), and decision rules (e.g., when vulnerability indicators exceed a prespecified threshold, prompt an activity suggestion). Additionally, JITAIs should target short-term goals called proximal outcomes (e.g., increased momentary activation and improved mood/well-being) that are related to long-term goals called distal outcomes (e.g., reduced depressive symptoms or increased well-being).

In this study, repeated EMA at decision points serves as the basis for tailoring: it captures momentary indicators of vulnerability and opportunity (tailoring variables). Together with prespecified decision rules, these variables determine whether an activity-suggestion prompt is delivered. These prompts are intended to facilitate the initiation of small, feasible, and personally meaningful activities, thereby interrupting withdrawal and avoidance cycles, and increasing contact with reinforcing experiences. This increased engagement is expected to incrementally improve momentary mood and well-being (proximal outcomes), and over time, lead to reductions in depressive symptoms (distal outcomes). Consistent with behavioral activation theory, the emphasis is on activation preceding mood improvement. Accordingly, activity initiation is targeted specifically during periods of vulnerability (i.e., low mood) where the risk of withdrawal or avoidance is high, rather than treating low mood as an indicator of readiness.

## Study aims and hypotheses

Because of the promising characteristics of JITAIs for behavioral activation in depression, our goal is to develop and evaluate JITAIs that target behavioral activation for depression. This will involve a design phase, in close collaboration with individuals with depression and therapists, and an evaluation phase to assess feasibility, acceptance, and preliminary effectiveness. We hypothesize that (1) it will be feasible and acceptable to deliver JITAIs to patients receiving treatment for depression, (2) JITAIs will result in improved proximal outcomes in terms of depression and well-being compared with not receiving JITAIs, and (3) behavioral activation with JITAIs will result in improved distal outcomes from baseline to post-treatment compared with TAU in terms of depression, well-being, personal recovery, and quality of life.

## Methods

### Design

This study uses a mixed-methods design that combines a participatory design phase with an evaluation phase. The design phase aims to develop JITAIs for behavioral activation in individuals with depression in collaboration with patients and therapists through focus groups. The evaluation phase consists of two components: a micro-randomized trial (MRT) to assess the proximal effects of JITAIs. In this component, randomization occurs at the within-participant level rather than between participants. Second, a nonrandomized quasi-experimental design to evaluate changes in between-group distal effects. The latter consists of a comparison of changes in mental health outcomes from baseline to post-treatment between JITAIs in addition to TAU and TAU only (comparator).

### Participants

#### Participants with depression

Participants will be recruited from a mental health institution in the Netherlands. For the design phase, a purposive sample of twelve participants with depression, including six participants with low literacy or low digital literacy, will be recruited. For the evaluation phase, 104 participants will be recruited: 52 for the treatment-as-usual with the JITAIs as add-on condition (TAU + JITAIs) and 52 for the treatment-as-usual (TAU) condition. The inclusion criteria for the participants in the evaluation phase are as follows: (a) age 18 years or older, (b) diagnosis of depressive disorder according to the DSM-5, (c) scheduled to start (cognitive) behavioral therapy for depression and (d) possession of an Android or iOS smartphone. The exclusion criterion is insufficient proficiency in Dutch to participate in the study and complete the questionnaires.

#### Therapists

The participating therapists will be recruited from the same mental health institution as the participants. Therapists include nurses, nurse practitioners, master-level psychologists, registered psychologists, or psychiatrists.

For the design phase, 4 therapists from different disciplines will be recruited. For the evaluation phase, 10 therapists will be recruited. In the evaluation phase, all participating therapists will attend a 2-h workshop explaining the JITAIs and the software application used for the JITAIs. At the end of the study, the therapists will be asked to discuss how they and their patients have experienced the JITAIs through a qualitative interview and a questionnaire [22].

## Measures

### Primary outcome

JITAIs are considered feasible when average dose-received adherence exceeds 60%, defined as the proportion of completed JITAIs among the total number of JITAIs received. This threshold was prespecified as a progression criterion for future evaluation. The percentage is based on a review of digital interventions for depression, in which a dose-received adherence higher than 60% was significantly associated with improved outcomes [23].

### Secondary outcomes

The following measures will be used to assess acceptance:*Client Satisfaction Questionnaire (CSQ-8)*. The CSQ-8 [24] is a questionnaire aimed at measuring satisfaction via 8 items. These items (e.g., “Would you like to use the JITAIs in the future?”) are scored on a 4-point Likert scale ranging from 1 to 4. A minimum score of 8 and a maximum score of 32 can be obtained for the CSQ-8. The scores are regarded as 'poor' when they fall between 8 and 13, ‘fair’ when they are between 14 and 19, ‘good’ when they are between 20 and 25, and ‘excellent’ when they are between 26 and 32.*System Usability Scale (SUS)*. The SUS [25] is a questionnaire measuring the usability of the JITAIs with 10 items. These items (e.g., are the JITAIs easy to use? and “I needed the help of a technical person to be able to use the JITAIs”) are scored on a 5-point Likert scale ranging from strongly disagree (0) to strongly agree (4). A minimum score of 0 and a maximum score of 40 can be obtained for the SUS. The total scores are multiplied by 2.5, and the total scores above 68 indicate acceptance of the system, with better acceptance scores between 70 and 90 and superior acceptance scores above 90.*Twente Engagement with Ehealth Technologies Scale (TWEETS)*. The TWEETS [26] is a questionnaire measuring engagement with e-health technologies with 9 items. The questionnaire consists of items on behavioral engagement (e.g., [this technology] is part of my daily routine), cognitive engagement (e.g., [this technology] makes it easier for me to work on [my goal]), and emotional engagement (e.g., I enjoy using [this technology]) and is scored on a 5-point Likert scale ranging from strongly disagree (0) to strongly agree (4). A minimum score of 0 and a maximum score of 36 can be obtained on the TWEETS, with a higher score indicating greater engagement. Participants who are engaged are more likely to have sum scores ≥ 27 [26].

JITAIs are considered acceptable when one of the following criteria is met: a CSQ-8 score ≥ 20, a SUS score ≥ 68, or a TWEETS sum score ≥ 27. The more criteria that are met, the more acceptable JITAIs are considered.

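### The SUS scoring rule as written gives points for agreement with a negatively worded item, and no reversal is stated

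*Protocol article*

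**What the plan says.** The scoring is described in the protocol article under Measures, Secondary outcomes. The scale has ten items: "The SUS [25] is a questionnaire measuring the usability of the JITAIs with 10 items". Two examples are given. In one, agreement is favourable ("are the JITAIs easy to use"); in the other, agreement is unfavourable ("I needed the help of a technical person to be able to use the JITAIs"). The sentence containing these examples goes on to give the item scores for both, and the raw range follows: "strongly disagree (0) to strongly agree (4). A minimum score of 0 and a maximum score of 40 can be obtained for the SUS". Then come the rescaling and the cut-off: "The total scores are multiplied by 2.5, and the total scores above 68 indicate acceptance of the system". Two higher bands are named, 70 to 90 as better and above 90 as superior.

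The section ends by calling the intervention acceptable if any one of three criteria is met, "a CSQ-8 score ≥ 20, a SUS score ≥ 68, or a TWEETS sum score ≥ 27", and more acceptable the more of them are met. The Acceptance paragraph under Data analyses adds only that the questionnaires will be summarised descriptively. Reverse scoring of SUS items is not mentioned in any section.

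**The concern.** The 0-to-4 direction is attached, in a single sentence, to two items that point opposite ways. For the item on needing technical help, strong agreement reports poor usability but earns the full 4 points, and strong disagreement reports good usability but earns none. A total built this way cannot consistently mean that higher is better, yet the 68 cut-off and both higher bands assume that it does.

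At stake is the SUS criterion itself, and through it the acceptability verdict. The Discussion names acceptability, together with dose-received adherence above 60%, as what would lead to a larger trial. Someone who programmed the score from this text would build one that is partly misdirected.

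**Working it through.** **Inputs, all from Measures, Secondary outcomes:** 10 items; item scores 0 to 4; multiplier 2.5; cut-off 68; at least one negatively worded item. The number of negatively worded items, k, is not given. The text shows k of at least 1, and larger values below are an assumption.

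**Step 1: the plan's own range.** 10 × 0 = 0 and 10 × 4 = 40; 40 × 2.5 = 100. The stated 0 to 40 is reproduced. It is the same with or without reversal, because a reversed item also runs from 0 to 4.

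**Step 2: distortion from one unreversed item.** For a response x on a negative item, the written rule contributes 2.5x and the reversed rule 2.5(4 − x). The difference is 2.5x − 2.5(4 − x) = 5x − 10. For x = 0 (no help needed) this is −10; for x = 1, −5; for x = 2, 0; for x = 4 (help clearly needed), +10.

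**Step 3: totals under the written rule.**
- Ideal user (4 on positive items, 0 on negative items): 2.5 × 4 × (10 − k) = 100 − 10k.
- Least favourable user (0 on positive, 4 on negative): 2.5 × 4 × k = 10k.
- Moderately favourable user (3 on positive, 1 on negative): 2.5 × [3(10 − k) + k] = 75 − 5k.

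With reversal the three totals are 100, 0 and 75 for every k.

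| k | Ideal | Least favourable | Moderately favourable |
|---|---|---|---|
| 1 (documented) | 90 | 10 | 70 |
| 2 (assumed) | 80 | 20 | 65 |
| 3 (assumed) | 70 | 30 | 60 |
| 4 (assumed) | 60 | 40 | 55 |
| 5 (assumed) | 50 | 50 | 50 |

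**Step 4: position against the cut-offs.** 68 / 2.5 = 27.2, so an individual needs a raw total of at least 28, which rescales to 70. At k = 1 the moderately favourable user has 9 × 3 + 1 = 28, the lowest total that passes. One who instead strongly disagrees with needing help has 9 × 3 + 0 = 27, which rescales to 67.5 and falls short; reversed, it is 27 + 4 = 31, or 77.5. So even with the one documented item, the better answer can move an individual below the line. The ideal user at k = 1 scores exactly 90 and so cannot enter the band above 90.

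Under the assumed larger k, the moderately favourable user falls below 68 from k = 2 (65) and the ideal user from k = 4 (60). At k = 5 the ideal and least favourable users both score 50.

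**The case against.** The strongest defence is that the sentence only describes the response format of a cited instrument. A condensed article may leave item reversal to that instrument's scoring instructions or to the full protocol, neither of which is shown. The authors plainly mean higher to be better. They also know about mixed item direction: in the Evaluation phase procedure they set opposite-direction thresholds for negatively and positively worded EMA items. On this view the team will score the SUS correctly whatever the article says.

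Much of that stands. Reversal may well be applied in practice, and a reader who inferred that the team has chosen unreversed scoring would be going beyond the text. What does not stand is that this is only a detail left out. The article gives point values, range, multiplier and cut-off, and it names a negatively worded item among those scored 0 to 4 for agreement. Followed exactly, that recipe scores the item in the wrong direction.

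Two further objections also stand. Only one negative item is documented, so a reader who concluded that a usable system must fail 68 would be relying on an assumed k; at k = 1 an ideal user scores 90 and passes. The practical reach is also short. The SUS is secondary, the primary adherence outcome is untouched, and a falsely low SUS cannot by itself make the intervention unacceptable if the CSQ-8 or TWEETS criterion is met. The reverse error keeps some force: because one criterion is enough, a falsely high SUS could produce an acceptable verdict alone.

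**Conclusion.** The point holds as a scoring rule stated in the wrong direction for a quoted item. Its documented size is up to 10 points either way on the 0 to 100 scale: 90 instead of 100 for an ideal user, and 70 instead of 75 for a moderately favourable one. Anything larger depends on further negatively worded items, which the article neither shows nor counts; each would cost an ideal user another 10 points.

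Two inferences should be avoided. The 0 to 40 range is not an error. Nor do the documents show that the go-ahead for a larger trial turns on this: the consequence is limited to one of three alternative secondary criteria and to the number of criteria met. The wording should still be corrected, because that criterion counts toward the acceptability verdict.

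**What to change.** Add one sentence to the SUS description: positively worded items are scored 0 (strongly disagree) to 4 (strongly agree), and negatively worded items are reverse-scored, 4 (strongly disagree) to 0 (strongly agree), before summing and multiplying by 2.5. Confirm that the scoring code applies this before the 68 criterion is evaluated.

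The cost is a sentence and, if reversal is not already coded, a line of code. The range, multiplier and cut-off stay as they are, and no extra data are needed: the correction can be made from the item-level responses.

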### Proximal outcomes

#### Ecological Momentary Assessment (EMA) survey

A total of 16 questions are included in the EMA questionnaire (see Table 1). The morning questionnaire begins with an assessment of rest (I feel rested) rated on a scale ranging from not at all (1) to very much (7). Four items assessing depressive symptoms, which are based on the PHQ-9, are related to mood and energy level (i.e., “I feel down”; “I feel tired”; “I feel listless”; “I feel energetic”) and two items concerning well-being (“I feel satisfied”; “I feel cheerful”) [27]. These mood and well-being items are also rated on a scale ranging from not at all (1) to very much (7). These momentary mood and energy items also serve as tailoring variables at decision points during the MRT. Importantly, these tailoring variables indicate vulnerability or opportunity states in which withdrawal or avoidance is more likely and external prompting may facilitate the start of a feasible activity, consistent with an activation-first behavioral activation model. Additionally, participants are asked about their current location (e.g., at home, at school), who they are with (e.g., alone, with family), what activity they were doing before the measurement (e.g., studying, working), and how they rate that activity on a scale from very unpleasant to very pleasant. In subsequent EMA assessments after the first one of the day, participants are asked if they performed a suggested activity (yes/no). If they answer no, they are asked for the reason (e.g., did not feel like it, did not have energy, was not convenient, or other). If they answer yes, they rate how pleasant the activity was (very unpleasant to very pleasant) and how much satisfaction it provided (none at all to very much). The evening questionnaire includes additional items: an assessment of overall activity level during the day on a scale from not active at all (1) to very active (7), an evaluation of the best moment of the day on a scale from very unpleasant to very pleasant, and an open field for comments. The evening survey serves as a reflection on the day rather than as a decision point (see procedure). Finally, daily step counts are passively collected once a day via the participants’ smartphone sensors, as higher daily step counts are an indication of improvement in depressive symptoms [28].

